# De-escalation of adjuvant radio(chemo)therapy for patients with HPV-positive head and neck squamous cell carcinoma: study protocol for a phase I trial to reduce late toxicity (DELPHI)

**DOI:** 10.1186/s12885-026-16050-x

**Published:** 2026-04-29

**Keywords:** Dose de-escalation, HNSCC, HPV, Oropharyngeal carcinoma, Phase I clinical trial, Radiotherapy

## Abstract

**Background:**

Patients with locally advanced head and neck squamous cell carcinoma are receiving adjuvant radio(chemo)therapy as standard of care, according to national guidelines. However, patients with human papilloma virus (HPV) driven oropharyngeal squamous cell carcinoma (OPSCC), are shown to have superior locoregional control (LRC) rates, suggesting that they are likely being overtreated. To date it is unknown, if and to which extent adjuvant radiotherapy can be safely reduced.

**Methods and design:**

The interventional multicentric DELPHI trial is investigating step-wise radiation dose reduction in patients with both p16-overexpressing and HPV16 DNA positive OPSCC. Depending on international clinical and histopathological risk factors, patients are being enrolled in the high-risk or intermediate-risk arm. Patients of the high-risk arm are receiving standard simultaneous chemotherapy with cisplatin. Patients with smoking history of at least 30 packyears are being treated in the observational arm.

Primary endpoint of the DELPHI trial is LRC after 24 months. Secondary endpoints are acute and late toxicity, quality of life during and up to 24 months after the end of therapy as well as LRC and overall survival after 60 months.

**Discussion:**

Primary aim of the DELPHI trial is to show that radiation dose reduction is safe and therefore feasible in patients with HPV-positive OPSCC. Secondary objective is to show that radiation-dose reduction leads to less late toxicity compared with standard treatment and thus improves quality of life.

**Trial registration:**

The DELPHI trial is registered at clinicaltrials.gov under the identifier NCT03396718.

**Supplementary Information:**

The online version contains supplementary material available at 10.1186/s12885-026-16050-x.

## Introduction/ rationale

Patients with locally advanced, resectable head and neck squamous cell carcinoma are receiving surgery, followed by standard adjuvant radio(chemo)therapy according to national and international guidelines. This has been established stepwise. First, it has been shown that dose escalation to the previous tumour bed as well as to cervical levels with lymph node metastases results in higher local control rates in patients with microscopical residual disease [1, 2]. However, dose escalation to more than 57 Gy was only beneficial in patients who are on high risk to develop recurrences, i.e. those with residual disease, large tumours, more than two regional lymph node metastases or lymph nodes with extracapsular extension (ECE). To further improve local control, the effect of simultaneous chemotherapy was studied within two clinical trials of the EORTC and the RTOG, which led to higher locoregional control rates, extended disease-free survival and longer overall survival of patients who received combined radiochemotherapy in comparison to those with adjuvant radiotherapy alone [3, 4]. This led to the current standard therapy of patients who are on high risk to develop recurrences, with doses up to 66 Gy and concurrent cisplatin-based chemotherapy. However, with increasing total radiation dose to the swallowing apparat and to the salivary glands the incidence of high grade late effects is rising [5, 6].

Well-known risk factors for the induction of HNSCC are smoking and alcohol consumption. In addition, infection with human papillomavirus (HPV) has been shown to particularly induce oropharyngeal squamous cell carcinoma (OPSCC) and over the last two decades the incidence of HPV-positive tumours has been increasing in the United States and in Europe [7, 8]. Furthermore, it has been shown that patients with HPV-positive disease have superior oncological outcomes and are also characterized by higher response rates after primary radiochemotherapy [9–14] and after adjuvant radiochemotherapy [15]. In Germany, patients with HPV-positive OPSCC often receive primary resection and, patients with high risk for recurrences according to established clinical risk factors, adjuvant radio(chemo)therapy. However, this multimodal treatment approach may lead to extensive late toxicities. While patients with HPV-positive OPSCC have a favourable prognosis and very high response rates to radio(chemo)therapy [9–14], thus likely becoming long-term survivors, they suffer from their chronic late toxicities.

Within the last decade, de-escalation of simultaneous chemotherapy has been investigated within clinical trials, with the overall aim to decrease toxicity in patients with OPSCC while maintaining high overall survival rates. However, after two randomised controlled clinical phase III trials showed a significant decrease in overall survival [16, 17] when replacing concomitant cisplatin by cetuximab without significantly reducing toxicity, cisplatin currently remains the standard therapy in patients with high-risk OPSCC.

The reduction of radiation dose with the overall aim to decrease chronic toxicities while maintaining excellent tumour control seems to be a promising strategy for improving therapeutic ratio in patients who are receiving adjuvant radio(chemo)therapy. A step-wise dose reduction within clinical trials is a straight-forward approach to find the optimal radiation dose for adjuvant treatment, which can then be studied within a randomised clinical trial in comparison to the current standard radio(chemo)therapy. Within the last years, clinical trials demonstrated that radiation dose de-escalation can be performed while maintaining high local control rates in patients with HPV-positive OPSCC. In a phase III study by Ferris et al. [18] in patients with intermediate risk for recurrences, dose reduction from 60 Gy to 50 Gy led to similar local control rates with 96% vs. 94,9% after 2 years. The AVOID phase II study in OPSCC patients with completely resected tumours (negative surgical margins at least 2 mm, no evidence of lymphovascular or perineural invasion) but lymph node metastases studied volume and dose de-escalation with respect to the previous tumour region. They showed that omission of adjuvant radiotherapy of the resected primary tumour region, while keeping the dose to the uninvolved neck regions (54 Gy total dose) and irradiation of the involved neck regions (60 to 66 Gy) leads to LRC of 98,3% after 2 years [19]. In a phase II study by Ma et al. [20], risk-adapted dose de-escalation to 30 to 36 Gy showed local control rates of about 96% after 2 years, which is comparable to historical control rates. Their recently published phase III trial provided randomised evidence that this substantial dose reduction resulted in decreased late toxicity [21]. However, this trial needs to be interpretated with caution. It was powered to detect differences in side effects, not oncological outcomes, and thus the trial does not allow to conclude that dose de-escalation to 30–36 Gy is safe in terms of disease control. Other clinical studies on dose- and/or volume-based de-escalation of adjuvant radiotherapy in patients with OPSCC are currently ongoing, e.g. as reviewed in [22, 23].

Proton therapy may also be an option to achieve high response rates with lower doses to organs at risk and therefore a potential reduction in late toxicities. Even though proton therapy is currently not widely available, it is allowed within the DELPHI trial presented here in order to open the possibility for comparison between both treatment modalities.

As mentioned above, smoking is one of the risk factors for the development of HNSCC. According to Ang et al. [24], cumulative nicotine abuse of more than 10 years may be associated with lower local control rates. However, this could not be confirmed by epidemiological studies or clinical data sets [25–27]. Within the current study, patients with a cumulative nicotine abuse of at least 30 packyears are being excluded from dose de-escalation and are enrolled in the observational arm.

Overall, patients with HPV-positive OPSCC are characterised by higher local control rates in comparison to those with HPV-negative disease. The hypothesis of our study is that moderate dose reduction does not lead to an increase of locoregional recurrences but results in less late side effects. Within this study, the HPV status is analysed centrally and includes p16 immunohistochemistry and HPV DNA genotyping. HPV-positive tumours are characterised by p16 overexpression of at least 70% of the tumour cells and HPV16 DNA positivity to ensure as much as possible that patients with truly HPV-driven tumour are being enrolled in the interventional arms [28].

Nevertheless, the potential risk of increased recurrences cannot be fully ruled out and is being monitored by several instances, including dummy runs of a treatment plan, quality control and central review of the first three treatment plans per center, central HPV analysis, stopping criteria of the study and step-wise reduction of the total dose including a monitoring time of 24 months of patients with intermediate- as well as in patients with high-risk disease.

The study protocol has been prepared in accordance with the SPIRIT (Standardised Protocol Items: Recommendation for Interventional Trials) guidelines [29].

## Study design

This is a multicentric, non-randomised phase I study, conducted at multiple academic university hospitals in Germany with expertise in head and neck oncology and radiotherapy. It consists of two interventional treatment arms and step-wise dose-reduction depending on risk factors for the development of recurrences. Allocation to the study arms is based on predefined clinical and histopathological risk factors and HPV status, as assessed centrally. Patients are enrolled in the high-risk arm if at least one of the following criteria is met: microscopically residual disease after resection, ECE of one or more lymph node metastases or large tumours (pT4) and a minimum of three lymph node metastases. For the intermediate-risk arm, patients with pT3 tumours or one to three lymph node metastases without any of the risk factors of the high-risk profile are included. Due to the nature of the intervention, blinding of participants and treating physicians is not feasible. The inclusion and exclusion criteria are summarised in Table 1. The schedule of enrolment, interventions and assessments is shown in the Supplementary figure.

**Table 1 Tab1:** Inclusion and exclusion criteria

Inclusion criteria:
• Oropharyngeal squamous cell carcinoma with indication of adjuvant radio(chemo)therapy
• ECOG performance status 0-1
• Experimental arm: HPV16(+) tumours
• Observational arm: HPV16(-) tumours
• Adequate compliance to ensure tumour follow-up care as per study protocol
• Age ≥ 18 years
• Written informed consent
• Neck dissection of at least tumour-bearing side

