**Additional inclusion criteria, high risk arm (at least 1 factor to be fulfilled):**
• R1 resection and/or
• pT4 status and/or
• > 3 lymph node metastases and/or
• Extracapsular spread of lymph node metastasis

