**Additional inclusion criteria for intermediate risk arm (at least 1 factor to be fulfilled):**
• pT3R0 and/or
• 1-3 lymph node metastases and no extracapsular spread of lymph node metastasis
Exclusion criteria:
• Cumulative nicotine abuse > 30 packyears for intervention arms. These patients are always included in control arms (regardless of HPV status).
• M1
• R2 resection
• No neck dissection performed
• >7 weeks interval surgery-radiotherapy
• Contraindication for guideline-compliant adjuvant radio(chemo)therapy according to clinical risk constellation
• Malignant tumour disease in the last five years before start of study (except basal cell carcinoma of the skin, in-situ carcinoma of the cervix uteri or breast or tumours with a similar good prognosis that are considered very likely to be cured)
• Any malignant tumour disease in the head and neck region regardless of interval and prognosis
• Previous radiotherapy with potential overlap
• Participation in another clinical trial if, and as result of this, another experimental therapy is necessary or the therapies/study protocols are mutually exclusive (e.g. modified chemotherapy, additional consolidating chemotherapy; immunotherapy). Additional participation in observational studies or supportive therapy studies are allowed
• Any other diseases or conditions that do not allow the patient to assess the nature and scope as well as possible consequences of the clinical study
• Pregnant or breastfeeding women

Dose de-escalation is performed in two steps with a dose-reduction by 10% each. The second dose de-escalation step is opened, when all of the planned 30 patients were accrued to the respective interventional arm, when at least 10 out of 30 patients finished their 24 months follow-up time and if the first stopping criterium (two recurrences within 24 months follow-up among the first 10 patients in the respective interventional arm) has not been reached. Patients enrolled after closure of the de-escalation arms, are being included in the observational arm and receive standard radio(chemo)therapy.

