The flowchart of the study is depicted in Fig. 1. Patients with operable OPSCC and indication for adjuvant radio(chemo)therapy, as recommended by the experts in the interdisciplinary tumour board for malignancies of the head and neck, are offered to participate in this clinical trial. After patient’s consent and consultation, FFPE tumour material is analysed centrally at the Institute of Pathology at the University Hospital Dresden and includes HPV analysis using p16 immunohistochemistry and PCR-array based HPV DNA genotyping. Patients with proven HPV-association of their tumours, e.g. positivity for both p16 (defined as continuous, strong block-type p16-positivity of the cytoplasm and/or nuclei in at least 70% of the tumour cells [24]) and HPV16 DNA (polymerase chain reaction (PCR)-array based analysis), are subjected to the interventional arm according to their risk for recurrences [intermediate-risk (IR) vs. high-risk (HR)] and treated with 10% dose reduction to both the former tumour bed and the lymph node levels. Patients without HPV-associated tumours are being allocated to the observational arm and are receiving standard radio(chemo)therapy within this prospective trial. After enrollment of 30 patients per risk-arm, patients are also being enrolled in the observational arm A or B (according to their risk profile) until a minimum follow-up of 2 years has been reached for 10 patients for the respective arm. For these patients, HPV is assessed but standard radio(chemo)therapy is applied irrespective of its result. The cohorts of the observational arms are serving as comparison group.

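### The node-count/pT4 rule and the 30-pack-year rule are each stated in two incompatible ways, so the same patient can be assigned to different arms

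*Protocol article*

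**What the plan says.** **Risk arm.** Under Study design, the text says that one criterion suffices for the high-risk arm. The last item in its list is "large tumours (pT4) and a minimum of three lymph node metastases". For the intermediate arm, the same paragraph says "patients with pT3 tumours or one to three lymph node metastases without any of the risk factors of the high-risk profile are included". Table 1 also requires at least one factor, but its high-risk list has pT4 as a separate item and "> 3 lymph node metastases and/or" as another. Its intermediate list has pT3R0 and, separately, "1-3 lymph node metastases and no extracapsular spread of lymph node metastasis".

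**Smoking.** The introduction says that patients with "cumulative nicotine abuse of at least 30 packyears are being excluded from dose de-escalation"; the abstract uses the same inclusive limit. Table 1 lists as an exclusion "Cumulative nicotine abuse > 30 packyears for intervention arms", which leaves exactly 30 eligible.

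**What the arm decides.** Table 2 gives different boost doses to the two risk arms and standard doses to the observational arm. The section on toxicities and quality of life gives cisplatin to all patients of the high-risk arms. The stopping limits are 2 recurrences in 10 patients, 3 in 20 and 3 in 30. Study design applies the first limit within the respective interventional arm and makes it a condition for opening step 2.

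**The concern.** Arm allocation here is entirely by rule. When two current statements of a rule disagree, two centres can each follow the article and treat identical patients differently.

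Three things are at stake. The first is the treatment the patient receives. The second is the make-up of the cohorts whose 24-month control is the primary result. The third is the recurrence count that drives stopping and the opening of step 2. With limits of 2 or 3 events, a single recurrence counted in one arm rather than another can decide whether a limit is reached.

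**Working it through.** **1. The planned figures reproduce.** Inputs from Statistics: looks at 10, 20 and 30 patients, limits 2, 3 and 3, recurrence rates 0.03 (expected) and 0.10 (maximum tolerated). P(stop) is the sum over looks of P(not stopped before, and cumulative recurrences at or above the limit).

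- Rate 0.03: the first look gives 1 − 0.97^10 − 10 × 0.03 × 0.97^9 = 0.0345. The later looks add 0.0099 and 0.0329. Total 0.0773, below the stated 0.1.
- Rate 0.10: 0.2639 + 0.1267 + 0.2216 = 0.6122, above the stated 0.6.

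The stopping design is therefore sound as calculated. The problem is who is counted in it.

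**2. Risk arm.** All profiles below are R0 without extracapsular spread. The text is read in two ways: the *and* as a separator between two criteria, or as a true conjunction. The text's rule that a patient with a high-risk factor cannot be intermediate is applied to the text columns.

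| Profile | Text, separator | Text, conjunction | Table 1 |
|---|---|---|---|
| pT2 or pT3, exactly 3 nodes | high | intermediate | intermediate |
| pT2, 4 nodes | high | neither arm | high |
| pT3, 4 nodes | high | intermediate | high (also meets the pT3R0 line) |
| pT4, 0 nodes | high | neither arm | high |
| pT4, 1 or 2 nodes | high | intermediate | high (also meets the 1-3 node line) |

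Under the separator reading, the conflict is at exactly 3 nodes. Under the conjunction reading, that conflict disappears, but pT4 alone and more than 3 nodes alone are then high risk only in Table 1. These are alternatives and must not be added together. No reading makes the text and Table 1 agree.

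**3. Smoking.** At exactly 30 pack-years, *at least 30* sends the patient to the observational arm and *more than 30* does not. Above and below 30 the statements agree.

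**4. Consequences, from Table 2 and the treatment text.**

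- Boost dose, high vs intermediate risk: step 1, 27 × 2.2 = 59.4 Gy vs 25 × 2.2 = 55.0 Gy; step 2, 25 × 2.2 = 55.0 Gy vs 22 × 2.2 = 48.4 Gy.
- Cisplatin: attached to the high-risk arms, so only the risk-arm contradiction changes it.
- At exactly 30 pack-years, within one risk group: step 1 boost of 59.4 Gy vs 64.0-66.0 Gy (high risk), or 55.0 Gy vs 58.0-60.0 Gy (intermediate risk).
- Stopping: the numerical limits are the same in both risk arms. A node or pT4 conflict changes which count the patient enters. The smoking conflict moves the patient between an arm with a stopping rule and one for which none is stated.

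**5. Effect on the stopping probability.** The article does not say how many patients are affected or how their recurrence rate differs, so no estimate is possible. Purely as an illustration with assumed values: suppose 10% to 30% of an arm were such patients with a recurrence rate of 0.06 to 0.10, and the rest stayed at 0.03. The arm rate would run from 0.9 × 0.03 + 0.1 × 0.06 = 0.033 to 0.7 × 0.03 + 0.3 × 0.10 = 0.051, and P(stop) from 0.09 to 0.22 instead of 0.077.

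**The case against.** The best defence is that Table 1 is described as a summary, that the Study design text contains a precedence rule, and that risk factors and HPV results go into a central eCRF that may already apply one rule. Much of this stands, and it rules out several stronger readings that a reader might infer.

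- *A patient with 3 nodes meets both arm definitions within the Study design text.* No. Intermediate risk there requires that no high-risk factor be present, so each reading of the *and* gives one arm. The conflict is between the text and Table 1.
- *Table 1 admits pT3R0 patients with extracapsular spread or more than 3 nodes to the intermediate arm.* Read alone, it does, but the precedence rule in the text settles this. Table 1 merely omits the rule.
- *The HPV rules contradict each other.* Table 1 says "Experimental arm: HPV16(+) tumours" without naming p16, while Study design speaks of "Patients with proven HPV-association of their tumours, e.g. positivity for both p16" together with HPV16 DNA. The abstract, introduction and Statistics use the same combined definition, and testing is central. The entry in Table 1 is plausibly shorthand.
- *HPV-positive patients have no stated route into the observational arm.* They have: Table 1 sends heavy smokers there whatever their HPV status, and Study design sends patients enrolled after an arm closes there too.
- *Patients face a different stopping boundary by risk arm.* The limits are identical; only the count differs.
- *One misplaced event raises the false-stop probability from 0.060 to 0.227.* These are P(X ≥ 3) and P(X ≥ 2) for 30 patients at rate 0.03. They compare two limits at a single look. Misallocation moves a patient between counts and does not lower the limit.

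The defence does not remove the two contradictions in the heading. The article does not say that the text prevails over Table 1, the text's own high-risk item is ambiguous, and the precedence rule cannot help until it is settled what counts as a high-risk factor. Nothing in the article resolves the pack-year inequality.

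**Conclusion.** Two contradictions stand in the current text: the node-count/pT4 rule, under either reading of the *and*, and the pack-year limit at exactly 30. Both are wrong as written and need correction, because each changes the treatment of identifiable patients and the recurrence count, if any, in which they are followed. The planned operating characteristics are unaffected as calculated. The size of the practical effect is unknown because the number of patients at these boundaries is not given; that 30 pack-years is a common rounded answer would be an assumption. The conclusion rests on taking the text and Table 1 as equally authoritative, and on no single rule in the eCRF being described. Recruitment is expected to run to the end of November 2027, so a correction can still protect future allocations.

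**What to change.** Reconcile the abstract, introduction, Study design text and Table 1 so that each of these is stated once and identically:

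1. the node count that defines high risk;
2. whether pT4 and node count are separate or joint criteria;
3. the pack-year inequality.

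Carry the precedence of high-risk factors from the Study design text into Table 1, and program the resulting rule in the eCRF. List patients already enrolled who have exactly 3 nodes, who have pT4 alone or more than 3 nodes alone as their only high-risk factor, or who reported exactly 30 pack-years, with the arm to which each was assigned. As a minor clarification, state in Table 1 that the HPV entry means p16 plus HPV16 DNA, if that is intended.

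Which cut-off or link is right is a clinical decision for the investigators. The cost is a clarifying amendment, one eCRF check and one listing. Sample size and stopping limits do not change.
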